### 6.3.1.7 Potential eye toxicity

Patients in the study are encouraged to maintain eye hydration, generally through the use of moisturizing eye drops. An ophthalmologist should evaluate visual complaints. Uveitis or episcleritis may be treated with topical corticosteroid eye drops. Atezolizumab should be permanently discontinued for immune-mediated ocular disease that is unresponsive to local immunosuppressive therapy. Ocular toxicity should be managed according to the guidelines in Table 7.

**Table 7. Guidelines for Managing Atezolizumab-Associated Eye Toxicity**

| Symptomatic eye toxicity (autoimmune uveitis, iritis, or episcleritis) | Management                                                                                                                                                                                                                                                                                                                                                                     |
|------------------------------------------------------------------------|--------------------------------------------------------------------------------------------------------------------------------------------------------------------------------------------------------------------------------------------------------------------------------------------------------------------------------------------------------------------------------|
| Grade 1-2                                                              | 
 
Evaluation by an ophthalmologist is strongly recommended
 
Treat with topical corticosteroid eye drops
 
Discontinue atezolizumab if symptoms persist despite treatment with topical immunosuppressive therapy
 
Topical immunosuppressive therapy
 
Contact PI if atezolizumab is discontinued.
 
 |
| Grade 3-4                                                              | 
 
Hold atezolizumab.
 
Start 60 mg prednisone or equivalent per day
 
Taper steroids over <math>\geq 1</math> month once symptoms improve to G0 or G1
 
Contact PI if atezolizumab is discontinued.
 
                                                                                                       |

### 6.3.1.8 Systemic Immune Activation

Systemic immune activation (SIA) is a rare condition characterized by an excessive immune response. Given the mechanism of action of atezolizumab, SIA is considered a potential risk. SIA should be included in the differential diagnosis for patients who develop a sepsis-like syndrome after administration of atezolizumab, and initial workup should include serum ferritin, complete blood count, LFTs, serum triglycerides, and a coagulation profile. In the event of suspected SIA, the PI's should be contacted for additional recommendations. Treatment with agents such as tocilizumab (anti-IL6), as well as corticosteroids, should be considered in the event of SIA.

### 6.3.1.9 Neurologic Disorders

Myasthenia gravis and Guillain-Barre syndrome have been observed with single agent atezolizumab. Patients may present with signs and symptoms of sensory and/or motor neuropathy. Diagnostic work-up is essential for an accurate characterization to differentiate between alternate etiologies. Neurotoxicity should be managed according to the guidelines in Table 8.

**Table 8 Management Guidelines for Neurologic Disorders**

| Autoimmune Neuropathy                       | Management                                                                                                                                                                                            |
|---------------------------------------------|-------------------------------------------------------------------------------------------------------------------------------------------------------------------------------------------------------|
| Grade 1                              | 

Continue atezolizumab, evaluate for alternative causes

                                                                                                |
| Grade 2                              | 

Hold atezolizumab.

Evaluate for alternative causes

Treatment should be as per institutional guidelines

                                |
| Grade 3-4                            | 

Permanently discontinue atezolizumab for life-threatening immune-related neuropathy

Treatment should be as per institutional guidelines

       |
| Myasthenia Gravis and Guillain-Barre | 

Permanently discontinue atezolizumab for myasthenia gravis or Guillain-Barre (all grades)

Treatment should be as per institutional guidelines

 |

### 6.3.1.10 Infusion-Related Reactions

No premedication is indicated for administration of cycle 1 of atezolizumab. Patients who experience an infusion-related-reaction (IRR) with cycle 1 of atezolizumab may receive premedication with antihistamines or antipyretics/analgesics (e.g. acetaminophen) for subsequent infusions. See table 9 for further advice.

**Table 9 Management Guidelines for Infusion-Related Reactions**

| Infusion Reactions | Management                                                                                                                                                                                                                                                                                                                                                                                                                                                                                                  |
|--------------------|-------------------------------------------------------------------------------------------------------------------------------------------------------------------------------------------------------------------------------------------------------------------------------------------------------------------------------------------------------------------------------------------------------------------------------------------------------------------------------------------------------------|
| Grade 1     | 
 
• Reduce infusion rate to half the rate being given at the time of onset.
 
• Once the event has resolved, the nurse should wait for 30 minutes while delivering the infusion at the reduced rate.
 
• If tolerated, the infusion rate may then be increased to original rate.
 
                                                                                                                                                              |
| Grade 2     | 
 
• Interrupt atezolizumab infusion
 
• Administer aggressive symptomatic treatment
 
• Restart only after the symptoms have adequately resolved to baseline grade
 
• The infusion rate at restart should be half of the infusion rate that was in progress at the time of the onset of the IRR
 
• At next cycle, administer oral premedication with antihistamine and anti-pyretic and monitor closely for infusion reaction
 
 |
| Grade 3-4   | 
 
• Stop infusion
 
• Proper medical management which may include oral or IV antihistamine, anti-pyretic, glucocorticoids, epinephrine, bronchodilators, and oxygen
 
• Discontinue atezolizumab and contact PI if atezolizumab is discontinued.
 
                                                                                                                                                                                              |

### 6.3.1.11 Immune-related myositis

Myositis or inflammatory myopathies are a group of disorders sharing the common feature of inflammatory muscle injury. Initial diagnosis is based on clinical (muscle weakness, muscle pain, skin rash in dermatomyositis), biochemical (serum creatine-kinase increase), and imaging (electromyography/MRI) features, and is confirmed with a muscle-biopsy. See table 10 for management guidelines of immune-related myositis.

**Table 10: management guidelines for Immune-related myositis**

| Immune-related myositis | Management                                                                                                                                                                                                                                                                                                                                                                                                                                                                                                                                                                                                                                                                                                                                                                                                                                                                                                                                                                                                                                                                                     |
|-------------------------|------------------------------------------------------------------------------------------------------------------------------------------------------------------------------------------------------------------------------------------------------------------------------------------------------------------------------------------------------------------------------------------------------------------------------------------------------------------------------------------------------------------------------------------------------------------------------------------------------------------------------------------------------------------------------------------------------------------------------------------------------------------------------------------------------------------------------------------------------------------------------------------------------------------------------------------------------------------------------------------------------------------------------------------------------------------------------------------------|
| Grade 1          | 
 
Continue atezolizumab
 
Refer patient to rheumatologists or neurologist
 
Initiate treatment as per institutional guidelines
 
                                                                                                                                                                                                                                                                                                                                                                                                                                                                                                                                                                                                                                                                                                                                                                                                                                                                                                   |
| Grade 2          | 
 
Withhold atezolizumab for up to 12 weeks after event onset
 
Refer patient to rheumatologists or neurologist
 
Initiate treatment as per institutional guidelines
 
Consider treatment with corticosteroid equivalent to 1-2 mg/kg/day IV methylprednisolone and convert to 1-2 mg/kg/day oral prednisone or equivalent upon improvement
 
If corticosteroids are initiated and event does not improve within 48 hours after initiating corticosteroids, consider adding an immunosuppressive agent.
 
If event resolves to Grade 1 or better, resume atezolizumab
 
If event does not resolve to Grade 1 or better while withholding atezolizumab, permanently discontinue atezolizumab
 
                                                                                                                                                                                                                                                                                                           |
| Grade 3          | 
 
Withhold atezolizumab for up to 12 weeks after event onset and contact Medical Monitor.
 
Refer patient to rheumatologist or neurologist.
 
Initiate treatment as per institutional guidelines.
 
Respiratory support may be required in more severe cases.
 
Initiate treatment with corticosteroids equivalent to 1 mg/kg/day IV methylprednisolone or higher-dose bolus if patient is severely compromised (e.g. cardiac or respiratory symptoms, dysphagia, or weakness that severely limits mobility); convert to 1-2 mg/kg/day oral prednisolone or equivalent upon improvement.
 
If event does not improve within 48 hours after initiating corticosteroids, consider adding an immunosuppressive agent.
 
If event resolves to Grade 1 or better, resume atezolizumab.
 
If event does not resolve to Grade 1 or better while withholding atezolizumab, permanently discontinue atezolizumab and contact Medical Monitor.
 
For recurrent events, treat as a Grade 4 event.
 
 |
| Grade 4          | 
 
Permanently discontinue atezolizumab and contact Medical Monitor.
 
Refer patient to rheumatologist or neurologist.
 
Initiate treatment as per institutional guidelines. Respiratory support may be required in more severe cases.
 
Initiate treatment with corticosteroids equivalent to 1-2 mg/kg/day IV methylprednisolone or higher-dose bolus if patient is severely compromised (e.g. cardiac or respiratory symptoms, dysphagia, or weakness that severely limiting mobility); convert to 1-2 mg/kg/day oral prednisone or equivalent upon improvement.
 
If event does not improve within 48 hours after initiating corticosteroids, consider adding an immunosuppressive agent.
 
If event resolves to Grade 1 or better, taper corticosteroids over > 1 month.
 
                                                                                                                                                                                                                             |

### 6.3.2 Carboplatin dose modification

#### Hematological toxicity

Treatment with carboplatin should be withheld if either of the following occurs within 24 hours prior to the administration:

- ANC is less than  $1 \times 10^9$ /l (G-CSF is not allowed)
- PLT count is less than  $100 \times 10^9$ /l.

Carboplatin will be restarted if hematological recovery occurs. Cycles will not be delayed but will be canceled, e.g. carboplatin will be administered during the first 12 weeks of the trial and not after this period and a cycle will not be given at a later date. Complete blood cell count should be repeated weekly until hematological recovery has occurred ( $ANC \geq 1 \times 10^9$ /l and  $PLT \geq 100 \times 10^9$ /l). No dose modification is allowed.

#### Renal toxicity

The combination of carboplatin with atezolizumab is not directly expected to cause renal toxicity. Therefore, no specific dose modifications are recommended for renal toxicity. However, the administered dose of carboplatin must be recalculated, based on a recalculated or re-measured eGFR for

- Renal toxicity (CTC grade 2, serum creatinine > 1.5 x ULN)
- Changes in serum creatinine of ≥10%
- Each dose modification of carboplatin
- Cycle 2, if there has been significant doubt about the true eGFR at cycle 1 (e.g. due to significant ascites)

#### Hypersensitivity to carboplatin

If there is a hypersensitivity reaction to carboplatin this should be managed as per local institutional protocols.

#### Peripheral neuropathy

If grade 2 toxicity develops, carboplatin should be held until neuropathy recovers (atezolizumab should continue as scheduled). If grade 2 neuropathy persists for > 2 weeks or recurs after carboplatin withhold, the patient will discontinue carboplatin treatment, but may continue atezolizumab.

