### Treatment

Carboplatin AUC 1.5 [17], intravenous administration, weekly schedule, maximum 12 administrations (no steroids necessary). After two administrations of carboplatin, atezolizumab (1200 mg flat dose) will be given in a 3-weekly schedule until tumor progression. Carboplatin will be administered before the atezolizumab infusion.

Carboplatin will be given for 12 weeks. If carboplatin has to be discontinued due to toxicity, atezolizumab can be continued as monotherapy.

Atezolizumab will be given until tumor progression or intolerable toxicity. After 12 months of atezolizumab treatment discontinuation is allowed in case of ongoing response or stable disease. At signs of progression after discontinuation of the treatment, atezolizumab can be re-started.

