### **6.2. Carboplatin**

Carboplatin is a platinum derivative and a highly polar molecule that does not readily diffuse across lipid membranes [38, 39]. In the high chloride environment of plasma, it remains largely in its native form, but once inside the cell, in which the chloride concentration is much lower, it becomes aquated and forms adducts with DNA and reacts with nucleophilic sites in a variety of targets [38]. Compared with cisplatin, carboplatin is essentially devoid of nephrotoxicity, and is less toxic to the gastrointestinal tract and less neurotoxic; by contrast, myelosuppression, principally thrombocytopenia, is dose limiting for carboplatin. Single-agent carboplatin is active in patients with previously untreated metastatic breast cancer, producing response rates of 20%-35%. [40]

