#### Other toxicities

If the patient develops any other grade 3 or 4 toxicity thought to be related to carboplatin, carboplatin should be held until symptoms resolve to ≤ grade 1 or baseline (atezolizumab treatment should continue as scheduled).

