#### 7.2.3 During weekly carboplatin administration (day 8 and 15 of cycle 1,2 and 3)

- ◆ Symptom directed physical exam
- ◆ Adverse events of grade  $\geq 2$  and the Adverse Events of Special Interest for atezolizumab
- ◆ Laboratory testing: hematology (Hb, leukocytes and differentiation, platelets), biochemistry (creat, urea, sodium, potassium, calcium, albumin, bilirubin,  $\gamma$ GT, AF, AST, ALT, LDH).

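### Section 6.3.2 ends carboplatin for grade 2 neuropathy that persists or recurs but sets no matching stop for grade 3-4, so worse neuropathy may be re-dosed or has no rule

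*Protocol*

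**What the plan says.** Two paragraphs of Protocol section 6.3.2 matter.

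- **Peripheral neuropathy.** If grade 2 develops, carboplatin is held until recovery. Then: "If grade 2 neuropathy persists for > 2 weeks or recurs after carboplatin withhold, the patient will discontinue carboplatin treatment". Atezolizumab may go on. Both the hold and the stop name grade 2 only.
- **Other toxicities.** For "any other grade 3 or 4 toxicity thought to be related to carboplatin", the instruction is that "carboplatin should be held until symptoms resolve to ≤ grade 1 or baseline". This paragraph sets no maximum hold, does not address recurrence, and contains no permanent stop.

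Section 4.1 (Treatment) allows atezolizumab to continue alone when carboplatin has to be discontinued for toxicity. It does not say which toxicity, at which grade or of what duration, requires that.

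**The concern.** A dose-modification scheme should become no more lenient as the toxicity grade rises. Here the only permanent carboplatin stop for neuropathy is tied to grade 2, and the text is silent on grades 3 and 4. A site that follows the wording could give carboplatin again after neuropathy worse than the kind that ends treatment, or could find no instruction at all.

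What is at stake is patient safety and uniform handling across the participating centres. The error rates and decision boundaries of the two-stage design are not involved.

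**Working it through.** No arithmetic applies, and the plan states no figure on this point. The check is to look for every rule that could govern carboplatin after grade 3-4 neuropathy and then to compare like courses.

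**Step 1. Is grade 2 shorthand for grade 2 or worse?** The protocol uses the ≥ sign where it means it: the dose-limiting toxicity list in section 4.2 is full of grade ≥3 entries, and section 7.2 records adverse events of grade ≥2. A literal reading of grade 2 in section 6.3.2 is therefore reasonable.

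**Step 2. Does another section supply the missing stop?**

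- Section 6.3 says the highest grade governs, but for several toxicities present at the same time. It adds no carboplatin stop for a single neuropathy.
- Table 8 in section 6.3.1.9 covers autoimmune neuropathy and directs atezolizumab only.
- The dose-limiting toxicity rules in section 4.2 apply to the first 5 weeks and lead to reporting and a discussion of the trial, not to a carboplatin stop in the individual patient.
- The sentence in section 4.1 on discontinuing carboplatin for toxicity sets no threshold.

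That leaves the Other toxicities paragraph as the only candidate.

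**Step 3. Compare like courses.** The last two columns are the two possible readings of the word other in that paragraph.

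| Course of neuropathy | Grade 2 | Grade 3-4, if the residual rule applies | Grade 3-4, if the residual rule excludes neuropathy |
|---|---|---|---|
| Lasts more than 2 weeks, then reaches grade ≤1 or baseline, with no more than 2 weeks at grade 2 on the way down (grade 3-4 case) | Permanent stop | Hold, then may resume | No written rule |
| Recurs at the same grade after a hold | Permanent stop | Held again, then may resume | No written rule |
| Starts at grade 3-4, then stays at grade 2 for more than 2 weeks | Not applicable | Grade 2 stop can apply | Grade 2 stop can apply |
| Starts at grade 3-4, then returns at grade 2 after the hold | Not applicable | Grade 2 stop can apply | Grade 2 stop can apply |

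**Result.** In the first two rows the worse grade has either the lighter rule or no rule. In the last two the existing wording can still end carboplatin, so the gap is limited to the first two.

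**The case against.** **The residual rule may not cover neuropathy.** It stands under a heading for other toxicities, after neuropathy has had its own paragraph. On that reading no lighter rule for the worse grade exists, and a sensible clinician would apply the grade 2 stop at least as strictly to grade 3-4. The reading is fair, and it means the inversion cannot be stated as certain. But it leaves no carboplatin rule above grade 2, which is no better.

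**Investigators can stop carboplatin anyway.** Section 4.1 expects discontinuation for toxicity in general, so repeated re-dosing after severe neuropathy would require an investigator who never used that route. This softens the practical risk. It does not close the gap, because no threshold is given.

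**The scenarios are narrow.** This stands. Carboplatin is given at AUC 1.5 for at most 12 doses, and section 6.2 calls it, compared with cisplatin, "less toxic to the gastrointestinal tract and less neurotoxic".

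**Two stronger inferences are not supported.**

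- A reader might want to count the extra carboplatin doses that grade 3-4 would allow. The protocol gives no time course for neuropathy, so any course length would be invented. It is also unclear whether missed doses can be made up. The rule that "carboplatin will be administered during the first 12 weeks of the trial and not after this period" stands under hematological toxicity, whereas section 6.3 lets a dose missed for a toxicity due to one component be given after the planned last one. A dose count would therefore not be established in either direction.
- A reader might also see a conflict with Table 8, because the neuropathy paragraph continues atezolizumab while Table 8 holds it at grade 2. Table 8 is for autoimmune neuropathy, and the paragraph sits in the carboplatin section. Section 6.3 lets the other drug continue when the toxicity is judged due solely to one component, and section 6.3.1.9 calls the diagnostic work-up essential. Read together, these already favour holding atezolizumab while the cause is unclear. At most a cross-reference would be a convenience.

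**Conclusion.** The concern holds in a limited form. Section 6.3.2 states a hold and a permanent carboplatin stop for grade 2 neuropathy and nothing specific for grade 3-4. Depending on how the word other is read, grade 3-4 neuropathy is either subject to a hold with no stop, or has no carboplatin rule. Under the first reading, two courses can be re-dosed where grade 2 of the same course could not: resolution with no more than 2 weeks spent at grade 2, and recurrence at grade 3-4.

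It would go too far to conclude that grade 3-4 neuropathy is always treated more leniently. An event that lingers at grade 2 for more than 2 weeks, or that returns at grade 2, can still trigger the stop.

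The conclusion rests on reading grade 2 literally, which the protocol's use of ≥ elsewhere supports. The number of patients affected cannot be computed, because no neuropathy incidence is given; it is probably small. No sample size, error rate, endpoint or stopping boundary changes. This is a safety wording that should be corrected because the correction is specific and cheap.

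**What to change.** In the Peripheral neuropathy paragraph of section 6.3.2, replace grade 2 with grade ≥2 in both places: the hold, and the permanent stop for persistence beyond 2 weeks or recurrence. Alternatively, keep the grade 2 wording and add that carboplatin is discontinued permanently at grade 3-4. The clinical team should choose between the two. Either version makes clear that neuropathy above grade 2 is not left to the residual rule alone.

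The cost is a wording change in one paragraph and earlier loss of carboplatin in a few patients with grade 3-4 neuropathy, who may continue atezolizumab alone as the protocol already allows. There is no statistical cost.
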